**Implementation**								
	**Perspective of webMFT^f^ intervention^g^**							
		Acceptability of webMFT	Study-specific questionnaire IAM^h^ (4-items) NPS^i^	✓	✓			✓
		Feasibility of webMFT	FIM^j^; 2-items: is webMFT easy to use? Doable?	✓	✓			✓
	Adaptations^k^		FRAME^l^		✓			✓
	Costs^k^		Cost tracking form	✓	✓			✓
	Fidelity^k^		Auditing of coach-delivered calls		✓			✓
	**Patient characteristics**							
		Patient demographics	Age, race, ethnicity, baseline level of MVPA^m^, cancer treatment status, and home address	✓			✓	
	**Organizational characteristics**							
		Organizational readiness	ORIC			✓	✓	

^a^RE-AIM: Reach, Effectiveness, Adoption, Implementation, Maintenance

^b^PRISM: Practical, Robust Implementation and Sustainability Model

^c^ORIC: Organizational Readiness for Implementing Change.

^d^ PI: principal investigator.

^e^MFT: Moving Forward Together.

^f^webMFT: Mentor1to1 web platform adapted for Moving Forward Together.

^g^Practical, Robust Implementation and Sustainability Model (PRISM) domains.

^h^IAM: Intervention Appropriateness Measure.

^i^NPS: Net Promoter Score.

^j^FIM: Feasibility of Intervention Measure.

^k^These measures will be tracked continuously throughout the study.

^l^FRAME: Framework for Reporting Adaptations and Modifications-Enhanced.

^m^MVPA: moderate to vigorous physical activity.

**Table 3 table3:** Qualitative data collection for Reach, Effectiveness, Adoption, Implementation, Maintenance (RE-AIM) and Practical, Robust Implementation and Sustainability Model (PRISM).

RE-AIM dimension, PRISM domain, and outcome				Description (interview^a^ questions)		Participant type				
						Survivors		Coaches		Organizational staff
**Reach**										
	**Perspective of webMFT^b^ intervention, survivor characteristics**									
		Motivation	What factors did you consider when you agreed to participate in webMFT? What motivated you, if anything, to stay in the intervention for the full 12 weeks? If you withdrew, why?		✓					
**Effectiveness**										
	**Perspective of webMFT intervention**									
		Program value	How did webMFT impact health and well-being of the survivors? What have you learned from participating in webMFT? How might webMFT benefit you?		✓		✓			
**Adoption**										
	**Perspective of webMFT intervention, Organizational Characteristics**									
		Motivation	What factors did you consider when you agreed to participate in webMFT? What motivated you to continue volunteering with webMFT?				✓		✓	
**Implementation**										
	**Perspective of webMFT intervention**									
		Acceptability of webMFT	Is webMFT acceptable? Did you like the intervention? What went well? What did not go well?		✓		✓		✓	
		Feasibility of implementing webMFT	Was webMFT feasible? What went well? What didn’t go well? Suggestions for improvements		✓		✓		✓	
		Patient centeredness	How did the intervention align (or not align) with the needs?		✓		✓		✓	
		Adaptations	What changes were made to webMFT during implementation?				✓		✓	
		Organizational readiness	How ready were you to implement webMFT?				✓		✓	
		Burden	Time and costs of implementation, unintended effects from webMFT		✓		✓		✓	
		Program fit	How does webMFT fit with your values and mission?						✓	
	**Organizational characteristics**									
		Climate and culture	Shared goals with webMFT; alignment with mission				✓		✓	
		—^c^	Data and decision support; workflow				✓		✓	
		Organizational readiness	Capacity to partner; What factored into your decision to partner to implement webMFT? What would have made it easier or harder to partner?						✓	
	**External environment**									
		—	Community resources, apps, local policies, access to safe places to recreate, urban or rural, access to Wi-Fi, insurance reimbursement, etc		✓		✓		✓	
	**Implementation infrastructure**									
		Implementation strategies	Coach training and support, resources, tools or skills Inclusion of webMFT roles into job descriptions and performance evals				✓		✓	
**Maintenance**										
	**Sustainability infrastructure**									
		Potential for sustainability	Intention to maintain webMFT; factors that would make it more sustainable (cost of delivery)				✓		✓	
		Motivation to sustain webMFT	Intention to continue, discontinue, or adapt webMFT delivery (coaches and staff); motivation to continue exercise behavior (survivors)		✓		✓		✓	

^a^Interviews will last approximately 45 to 60 minutes.

^b^webMFT: Mentor1to1 web platform adapted for Moving Forward Together.

^c^Not applicable.

#### Effectiveness

Intervention effectiveness, operationalized as changes in survivors’ MVPA (primary outcome), will be assessed at the postintervention time point (3 months; Table 1).

Postintervention assessments will follow the same procedures as at baseline: the questionnaires will be completed via REDCap and staff members conducting assessments will be blinded to the survivors’ group assignments. Staff members will mail the accelerometer to the patients. When the units are returned by mail and web-based questionnaires completed, survivors will receive a US $25 gift card (US $25×2 assessments=US $50). The assessments are described in Tables 1 and 3 and include the following:

Accelerometer: we will use the Actigraph accelerometer (GT3X) as a device-based and gold standard measure of MVPA. Survivors will be asked to wear the unit around their waist during all waking hours over a 7-day period. The Actigraph will be worn at baseline and the postintervention time point. The Freedson cut points [30] will be used to score the data; data will be collected in 10-second epochs. A valid accelerometer day is defined as >10 hours per day; participants are required to have 4 valid days of wear.QOL, physical functioning, fatigue and mood will be assessed using validated and standardized questionnaires that have been used by patients with breast cancer. Survivors will be asked to complete the following standardized questionnaires via REDCap: Functional Assessment of Cancer Therapy Scale-Breast [31], a 36-item Short Form Health Survey that includes a Physical Functioning subscale [32], Functional Assessment of Cancer Therapy Scale-Fatigue [33], and the Profile of Mood States [34]. In addition, the following questionnaires will be used to assess the constructs relevant to the TTM and SCT: Stage of Readiness for Exercise [35] and Exercise Self-Efficacy [36].Program value will be assessed during semistructured interviews at the study end with survivors to understand how webMFT impacted the health and well-being of the survivors (Table 3).

#### RE-AIM Implementation Outcomes

##### Reach

Reach will be assessed at the level of the survivor and will include the number of survivors eligible to participate out of the total potential survivors at participating organizations as well as the number of survivors excluded [18,37]. Furthermore, survivors will be asked about factors that influenced their motivation to join the program during semistructured interviews conducted at the postintervention time point (refer to Tables 2 and 3 for additional details).

##### Adoption

Adoption will be assessed at the level of the organization and the level of the coach and will include the total number of eligible organizations out of the total number of potential organizations, the percentage of eligible organizations that agree to participate in the study, as well as the percentage of eligible coaches who agree to participate to deliver webMFT [18,37]. In addition, coaches and organizational staff will be asked about factors that influenced their decision to participate in the study during semistructured interviews (refer to Tables 2 and 3 for additional details).

##### Implementation

On the basis of RE-AIM, the implementation dimension includes measures of the costs of delivering webMFT, as well as the fidelity of delivery and adaptations needed to feasibly deliver the program in an acceptable way to end users [18]. Accordingly, we have also grouped our assessment of feasibility and acceptability outcomes in this RE-AIM dimension, as well as the assessment of organizational readiness that relates to the feasibility of program delivery.

Implementation outcome measures of acceptability and feasibility of webMFT will be assessed at the postintervention time point (3 months). In addition, we will track adaptations to webMFT, costs of delivering webMFT, and fidelity to the program throughout the implementation of webMFT. Organizational readiness will be assessed at the level of the organization. Finally, we will collect several qualitative assessments of additional implementation outcomes based on the PRISM domains [18], through semistructured interviews with survivors, coaches and organizational staff members (Table 3). These assessments are described in Tables 2 and 3 and include the following:

Acceptability and feasibility: at 12 weeks, the survivors randomized to webMFT group and the coaches will evaluate the intervention components (eg, usefulness of calls and satisfaction) via a REDCap questionnaire [29,38] and during semistructured interviews. At the end of their study participation, all coaches will complete an evaluation (using REDCap) of the components of webMFT using a feedback questionnaire similar to the one used in prior trials, with additional items that focus on the web platform. Coaches will complete evaluations (on a 1-4 rating scale, 1=not at all satisfied; 4=very satisfied) of satisfaction and acceptability of each webMFT component (eg, viewing patient’s MVPA) in REDCap. We will also evaluate the number and duration of the calls delivered (tracked by the web platform) and barriers identified by the coaches on the feedback questionnaire. Furthermore, both survivors and coaches will complete additional quantitative measures including the 4 items from the Intervention Appropriateness Measure [39], 2 items from the Feasibility of Intervention Measure—is the intervention (1) easy to use and (2) doable? [39]—and the Net Promoter Score [40,41]. During intervention delivery, coaches will be interviewed to explore their experiences with webMFT and to elicit suggestions for improvements. These data will be used to modify webMFT at the end of the study.Adaptations: adaptations to webMFT will be assessed at the level of the coach and the level of the organizational staff. We will track adaptations throughout the duration of the implementation of webMFT based on a survey adapted from the Framework for Reporting Adaptations and Modifications-Enhanced (FRAME; Table 2) [42] and using qualitative methods (Table 3).Costs: we will assess patient costs as in prior studies [27] to capture out-of-pocket expenses and any health care costs related to MVPA. We will also assess the costs for coach training or intervention delivery, using established time-based activity costing techniques [43]. We will use the quantitative data to inform the development of debrief questions and recontact a subgroup of webMFT survivors (n=20, randomly selected) and conduct interviews to understand the patient perspective of webMFT and elicit suggestions for improvements, based on RE-AIM dimensions and PRISM domains. The time taken by the coaches to deliver webMFT (ie, for preparation, delivery, and follow-up of calls) will be tracked on the web platform and during biweekly calls with the project director. These data along with the time spent in training and supervision will allow us to estimate costs to the coaches, a key issue in designing for dissemination [44].Fidelity: intervention fidelity will be assessed using auditing of the coach-delivered calls as has been done in prior work [11-13]. The principal investigator will audit 10% of completed coach calls throughout the duration of implementation of webMFT.Organizational readiness: we will conduct brief surveys (assessing demographics and prior experience with research collaborations) and telephone-based interviews with key individuals in each partner organization. Each potential organization will also be asked to complete the Organizational Readiness for Implementing Change questionnaire [45]. We anticipate interviewing 4 to 6 individuals (1-2 per organization) such as the peer supervisor. Semistructured interviews will be scheduled at a time that is convenient for the interviewee, will last approximately 45 to 60 minutes, and will be audio recorded. A research team member will conduct the interviews and use a semistructured interview guide to ensure that each interviewee is asked the same core questions, based on PRISM domains.

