### Sample Size

Power calculations were based on data from our prior work with MFT [27], and data from the study by Cadmus-Bertram et al [28], who compared web-based tracking+Fitbit to pedometer alone among postmenopausal women. Comparing the effects of coach counseling [27] to web-based tracking+Fitbit [28] on changes from baseline in MVPA would yield a medium effect size, *d*=0.60. Assuming similar effect sizes and a 2-sided α=.05, we would have more than sufficient power to test intervention effects on changes in MVPA (minutes per week) at the end of intervention with 20 survivors per arm. However, given the risk of powering on pilot studies, we have conservatively inflated the sample size to 25 survivors per arm. On the basis of our prior work, we expect attrition to be ≤10% at 12 weeks, so we will recruit a total of 56 women (n=28 survivors per arm) to obtain complete data from 50 survivors.

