#### Training Coaches

Before beginning training, coaches will receive a training manual. On the basis of prior work, we will develop recorded training modules that provide information on the benefits of exercise for survivors of cancer; TTM and SCT; training on counseling techniques (eg, empathy and reflective listening); working with human participants and HIPAA regulations; and emergency protocols. In addition, trainers will offer 1 live internet-based group training session during which coaches will practice role plays and receive feedback through videoconferencing. Coaches will complete a second live internet-based individual training session to ensure that they can deliver the intervention while using the platform, using screen sharing capabilities between the coach and research staff. Coaches will be trained to query patients at each call about health symptoms and notify the research staff immediately if survivors endorse any symptoms that are potentially indicative of a serious problem. In these cases, study participation will be temporarily halted until the medical issue has been resolved. Coaches will receive a supervision call every other week from research staff members through the web platform.

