## Results

As of September 2023, phase 1 of the study was completed, and 61 survivors were enrolled in phase 2. We expect that using newer technologies for enhanced intervention delivery, program management, and automated data collection may facilitate effective implementation by organizations with limited resources. Adapting evidence-based MFT to a customized web platform and collecting data from coaches, survivors, and organizations along with costs will provide the basis for an implementation trial to increase MVPA and its benefits among many more survivors of breast cancer.

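### A simple random draw of 20 webMFT women for interview does not ensure that the few who withdraw are asked why; inviting them first is a cheap, minor improvement

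*Protocol article*

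**What the plan says.** The protocol article gives four relevant pieces.

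- **The question.** Table 3, Reach, Motivation row, includes "If you withdrew, why" among the interview questions. Only the survivor column is ticked.
- **The selection rule.** Under RE-AIM Implementation Outcomes, Implementation, the Costs item says the team will "recontact a subgroup of webMFT survivors (n=20, randomly selected" and interview them about the patient perspective, structured by RE-AIM dimensions and PRISM domains. Table 3 is built on the same structure.
- **The numbers.** The Sample Size section states: "we expect attrition to be ≤10% at 12 weeks, so we will recruit a total of 56 women (n=28 survivors per arm", the aim being "to obtain complete data from 50 survivors". The Results section reports that "61 survivors were enrolled in phase 2" by September 2023.
- **Other statements on survivor interviews.** Three places mention semistructured interviews with survivors without a limit of 20: the program value item under Effectiveness, the Reach paragraph, and the opening of the acceptability and feasibility item under Implementation.

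Table 2 tracks why survivors were excluded and why eligible survivors declined. It has no row for why enrolled women withdrew.

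**The concern.** Very few women in the arm can answer the withdrawal question, and their number is not known in advance. A simple random draw treats them like everyone else, so whether each is asked is left to chance. With two or three such women, missing one loses a third to a half of the first-hand information on why women leave the program.

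This matters because the Overview under Data Analyses says that survivor debrief interviews, together with coach feedback, will be used to revise webMFT before a larger trial. The primary outcome and its analysis are not affected.

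**Working it through.** **Inputs.** Arm size N = 28 and attrition of at most 10% (Sample Size); interviews n = 20, drawn at random from webMFT (Implementation, Costs item).

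**The plan's own figure.** 25/(1 − 0.10) = 27.8, rounded up to 28 per arm. 50/(1 − 0.10) = 55.6, rounded up to 56. Both reproduce.

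**Expected withdrawals.** 10% of 28 = 2.8, so up to about 3 in webMFT if attrition is equal in the two arms.

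**Chance for one woman.** 20/28 = 71.4% selected and 28.6% not selected, whether or not she withdrew.

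**Chance for w withdrawn women (hypergeometric).** P(all selected) = C(N − w, 20 − w)/C(N, 20). P(none selected) = C(N − w, 20)/C(N, 20). P(at least one missed) = 1 − P(all selected).

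| w | P(all selected) | P(at least one missed) | P(none selected) |
|---|---|---|---|
| 1 | 20/28 = 0.714 | 0.286 | 8/28 = 0.286 |
| 2 | (20·19)/(28·27) = 0.503 | 0.497 | (8·7)/(28·27) = 0.074 |
| 3 | (20·19·18)/(28·27·26) = 0.348 | 0.652 | (8·7·6)/(28·27·26) = 0.017 |

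**Expected number selected when w = 3.** 3 × 20/28 = 2.14. Inviting all three first therefore gains 3 − 2.14 = 0.86 of a woman on average.

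**Sensitivity to the reported enrolment.** If all 61 enrolled women were randomized 1:1 (an assumption), the arm holds 30 or 31. The chance of selection is then 20/30 = 66.7% or 20/31 = 64.5%. With 3 withdrawals, at least one is missed with probability 0.719 or 0.746, and none is selected with probability 0.030 or 0.037.

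**The case against.** Much of the case on the other side stands, and it sets the limits of this point.

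- A reader might infer that the debrief is the only enquiry into harm or tolerability. It is not. The Burden row of Table 3, "Time and costs of implementation, unintended effects from webMFT", is ticked for survivors, coaches and organizational staff. The Training Coaches section adds: "Coaches will be trained to query patients at each call about health symptoms and notify the research staff immediately". Calls are also recorded, and 10% of completed calls are audited.
- A reader might infer that women whose participation is halted for symptoms are lost in the same way. Halts are described as temporary, and staff are told at the time, so knowledge of these events does not depend on the draw.
- A reader might infer that withdrawn women are likely to be left out. Under a random draw from the whole arm, each is more likely in than out. That reading would need a frame of completers only, or lower response among withdrawn women. The article states neither. Lower response is plausible but is an assumption, and changing the selection rule would not cure it.
- The article's silence does not show that withdrawal reasons go unrecorded. The full protocol is not shown and may provide for recording them when a woman leaves.
- The statements on survivor interviews without a limit may mean that all webMFT women are interviewed, with the 20 as an additional debrief. The article does not say whether these are the same interviews, so a reader cannot tell whether a given withdrawn woman will be asked. This calls for clarification rather than removing the point.
- Random selection has a merit of its own: staff cannot pick favourable interviewees. The fix should keep that protection.

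**Conclusion.** The point holds as a minor, inexpensive improvement, limited to reasons for withdrawal. The stated rule does not ensure that withdrawn women are asked a question written for them. With 2 or 3 withdrawals, at least one is missed with probability of about 50% or 65%. A complete absence of answers is unlikely: 7.4% with 2 withdrawals and 1.7% with 3.

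These figures assume 28 women in the arm, a frame of all women randomized to webMFT, no differential refusal, and that the draw of 20 governs the Table 3 survivor interviews. If all webMFT women are in fact interviewed, only the need to reconcile the wording remains.

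**What to change.** Change the selection rule and keep the count at 20:

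1. State that the sampling frame is all women randomized to webMFT, including those who withdrew.
2. Invite every woman who withdrew first.
3. Fill the remaining places at random from the others. With 3 withdrawals who all accept, that is 17 drawn from 25.
4. Report the two groups separately.
5. Reconcile the figure of 20 with the survivor-interview statements under Effectiveness, Reach, and acceptability and feasibility, so that it is clear who is interviewed and on what.

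The cost is a sentence or two, with the same number of interviews and the same staff. The 20 would no longer be a simple random sample. That matters little for the thematic analysis planned under Analyses of Qualitative Data, and the random portion still keeps staff from choosing the interviewees.

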
##### Maintenance

Potential for sustainability and motivation to sustain webMFT will be assessed during the semistructured interviews with survivors, coaches, and organizational staff (Table 3).

### Data Analyses

#### Overview

We will examine RE-AIM dimensions (Tables 1-3) to guide us in assessing the potential for larger-scale implementation of webMFT. We will conduct descriptive analyses of reach, adoption, and implementation outcomes including acceptability and feasibility of webMFT (eg, the number and mean duration of calls, barriers, and perceived feasibility of intervention delivery as judged by coaches). According to the current recommendations [46], we will consider webMFT feasible if >75% of the scheduled calls are delivered and survivor and coach and acceptability or satisfaction exceed 80% on rating scales (ratings of “moderately” to “very satisfied/acceptable”). Feedback from coaches and survivor debrief interviews will be used to revise and update webMFT for a larger-scale implementation trial.

We will assess potential between-group differences (webMFT vs MVPA tracking) in baseline variables (eg, age and medical history) using graphical methods, nonparametric and parametric tests as appropriate (eg, Wilcoxon rank-sum test for skewed data, 2-tailed *t* tests for normally distributed continuous data, and chi-squared tests for categorical data). Any variables not balanced by randomization will be controlled for as covariates in subsequent analyses, provided they are significantly associated with the outcome under consideration (at a modest *P*<.10 level).

We will assess effectiveness by examining the effects of webMFT versus MVPA tracking on the change in survivors’ MVPA in minutes per week (accelerometer data) at 12 weeks (3 months) using a mixed effects regression model, in which we will regress MVPA at 12 weeks on baseline MVPA, randomized group, wear time, and any variables not balanced by randomization. Models will include random intercepts to adjust for repeated measures within the participant over time. We will use a similar approach to estimate the effects of group on mood, QOL, physical function, and fatigue at 12 weeks. The interest is in estimating effect sizes and CIs. Analyses will be conducted on the intent-to-treat sample with all randomized participants included. Mixed effects models use a likelihood-based approach to estimation and do not require any direct imputation of missing outcomes.

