#### Random Assignment

Survivors will be randomly assigned to a group after informed consent and baseline data are obtained. Consistent with prior work, the sample will be stratified for 2 variables that may affect MVPA outcomes (age: <60 years or >60 years; and treatment: received or not received chemotherapy). The randomization scheme will be generated using the R (the R Foundation for Statistical Computing), based on a permuted block randomized procedure with small, random-size blocks so that equal numbers of survivors are randomized to webMFT or MVPA tracking by age and treatment. The project director will contact the survivor and disclose the group assignment from a sealed envelope.

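### The outcome models omit the two stratification factors, and the covariate rule can practically never add them; if the factors are prognostic, the reported standard errors are too large

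*Protocol article*

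**What the plan says.** Under Random Assignment, the protocol article says that "the sample will be stratified for 2 variables that may affect MVPA outcomes". The two variables are age group and receipt of chemotherapy. Small permuted blocks of random size are used "so that equal numbers of survivors are randomized to webMFT or MVPA tracking by age and treatment". The age strata are given as "age: <60 years or >60 years".

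Under Data Analyses, Overview, baseline variables are compared between arms "using graphical methods, nonparametric and parametric tests as appropriate", with no threshold for calling a variable unbalanced. The rule that follows is "Any variables not balanced by randomization will be controlled for as covariates in subsequent analyses, provided they are significantly associated with the outcome", the association being judged at P<.10. The next paragraph writes out the primary model: "we will regress MVPA at 12 weeks on baseline MVPA, randomized group, wear time, and any variables not balanced by randomization". Mood, quality of life, physical function and fatigue are to be handled in a similar way. Neither stratification factor is named as a covariate anywhere in the article.

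**The concern.** The design and the analysis pull in opposite directions. The design picks out two variables as possibly prognostic and forces the arms to agree on them. The analysis then admits extra covariates only if the arms disagree on them. The factors most deliberately balanced are therefore the ones least able to enter the model.

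This matters because stratified randomization removes from the treatment contrast the variation due to the stratification factors. A model without those factors leaves that variation in its residual error. If the factors are prognostic, the model overstates the uncertainty of the estimate: intervals are too wide and the test rejects too rarely under the null. The Overview gives estimation of effect sizes and confidence intervals as the interest of these analyses, and aim 3b uses the estimates to plan a larger trial, so interval width is part of what the trial is meant to deliver.

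The article states both the rule and the model terms. This is a choice it has made, not a detail it leaves to an analysis plan.

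**Working it through.** **Inputs from the protocol article.** Sample Size: an effect that "would yield a medium effect size, *d*=0.60", two-sided alpha .05, 25 completers per arm, attrition up to 10%, 56 recruited. Random Assignment: two binary factors, small permuted blocks within strata. Overview: the model terms and the covariate rule.

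**Input assumed.** R2 is the share of the 12-week MVPA variance left after baseline MVPA that the two factors jointly explain. The documents give no value, so it is run over a range.

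**1. The plan's own figure.** 50 / 0.90 = 55.6, rounded up to 56; 25 / 0.90 = 27.8, rounded up to 28 per arm. The recruitment total reproduces.

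**2. Can the rule select the factors?** In 10,000 simulated trials of 56 women, with blocks of 2 or 4 in the four age-by-chemotherapy strata, a chi-squared test flagged neither factor at .05 or at .10. In the runs with 50 women (step 4), the smallest P value seen for either factor was about 0.33, so any plausible threshold gives the same answer. If age is tested as a continuous variable (assumed mean 58, SD 10), it is flagged in 0.15% of trials at .05 and 0.9% at .10, before the outcome-association condition is applied.

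**3. Expected size.** Leaving out balanced factors that explain R2 of the residual variance raises the reported SE, relative to the model with them, by the ratio 1 / sqrt(1 − R2):
- R2=0.05: 1 / sqrt(0.95) = 1.026
- R2=0.10: 1 / sqrt(0.90) = 1.054
- R2=0.20: 1 / sqrt(0.80) = 1.118

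**4. Simulation.** There were 6,000 trials per setting, with 25 per arm on average, each factor at 50% prevalence and R2 split equally between them. The analysis was ANCOVA on baseline, with d=0.60 in SD units of the variance left after baseline. Wear time and attrition were not simulated. The effect of each factor is 2 × sqrt(R2/2): 0.32, 0.45 and 0.63 SD for R2 of 0.05, 0.10 and 0.20.

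| R2 | Mean SE without / with | Ratio | Power without / with | Type I error without / with |
|---|---|---|---|---|
| 0 | 0.285 / 0.285 | 1.00 | 53% / 53% | 5.1% / 5.1% |
| 0.05 | 0.285 / 0.278 | 1.025 | 54% / 56% | 4.6% / 5.0% |
| 0.10 | 0.285 / 0.270 | 1.05 | 54% / 57% | 3.7% / 4.8% |
| 0.20 | 0.285 / 0.255 | 1.12 | 55% / 63% | 3.0% / 5.4% |

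In every setting, a chi-squared screen of the two factors at .05 gave the same rejection rate as the model without them, because it never selected either. A second simulation gave power without and with the factors of 53% and 53%, 53% and 55%, 54% and 58%, and 54% and 63%. The gaps are therefore about 0, 2, 4 and 8 to 9 points. The Monte Carlo standard error of one power figure is about sqrt(0.25 / 6000) = 0.6 points.

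**5. Where the error lies.** At R2=0.20 the actual SD of the estimate is 0.260 without the factors and 0.257 with them, so the estimate is about equally precise either way. The reported SE is 0.285 without them, about 10% above the actual SD (0.285 / 0.260 = 1.10), and 0.255 with them, which agrees with it.

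**The case against.** The strongest reply is that the loss is conditional and may be small. Baseline MVPA, probably the best predictor, is already in the model, and the article says only that the factors might affect MVPA. At R2=0 nothing is lost; up to R2=0.10 the loss is at most about 4 points of power. The error is also in the cautious direction. All of this stands. It limits the size of the point, but does not remove the mismatch between design and model.

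Four stronger readings are tempting, and the documents do not support them.

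- *That power is certainly lost, or the estimate biased.* Neither follows. The loss depends on a prognostic strength that is not given, and the factors are balanced, so leaving them out does not shift the estimate.
- *That the selection rule does material harm of its own.* In a simulation with eight further baseline variables and effects of 0.5 SD per factor, the full two-step rule gave 54.1% power and 3.8% type I error, against 55.6% and 4.2% with no added covariates. Nearly all of the shortfall against prespecified strata (62.0% power) came from omitting the strata.
- *That the Overview states two conflicting rules.* The model sentence adds "baseline MVPA, randomized group, wear time, and any variables not balanced by randomization" without repeating the association condition, but it comes directly after the paragraph that sets the condition and can be read as referring back to it.
- *That the age strata are part of this fault.* As written they leave no place for a woman aged exactly 60, but that is a separate wording slip, perhaps a dropped equals sign, and has no bearing on the standard error.

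**Conclusion.** The point holds in a limited form. Two factors that the trial randomizes by are missing from its stated outcome models, and the stated route for adding covariates is closed to them in practice. That much rests on the text and on the blocking, not on any assumed effect.

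The consequence rests on the assumed R2. If the factors carry prognostic information beyond baseline MVPA, the reported standard error is too large by an amount that runs from nothing at R2=0 to about 12% (relative to the model with the factors) at R2=0.20. Type I error then falls to about 3%, and power at d=0.60 is up to 8 to 9 points lower than it need be. Confidence is high in the omission and moderate in the size of its effect. The change is worth making because it is almost free and serves the trial's aim of estimation.

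**What to change.** In Data Analyses, Overview, fix one covariate set in advance for every outcome: the baseline value of that outcome, randomized group, age stratum and chemotherapy stratum. Keep wear time in the accelerometer MVPA model, where the article already specifies it. Replace the baseline-imbalance and P<.10 screen with this set, describe baseline characteristics by arm, and put any further covariate in a labelled sensitivity analysis. As a minor accompanying step, state which age stratum holds women aged exactly 60, following how they were actually randomized.

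The cost is a sentence or two and 2 degrees of freedom (47 to 45 in the simulated model). Even at R2=0 the mean SE rises only from 0.2844 to 0.2849. No new data are needed, since both factors are recorded in order to randomize. The change should be settled before outcome data are analysed.
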